## Abstract

**Background:**

Despite evidence of benefit for pharmacist involvement in chronic disease management, the provision of these services in community pharmacy has been suboptimal. The Promoting Action on Research Implementation in Health Services (PARiHS) framework suggests that for knowledge translation to be effective, there must be evidence of benefit, a context conducive to implementation, and facilitation to support uptake. We hypothesize that while the evidence and context components of this framework are satisfied, that uptake into practice has been insufficient because of a lack of facilitation. This protocol describes the rationale and methods of a feasibility study to test a facilitated pharmacy practice intervention based on the PARiHS framework, to assist community pharmacists in increasing the number of formal and documented medication management services completed for patients with diabetes, dyslipidemia, and hypertension.

**Methods:**

A cluster-randomized before-after design will compare ten pharmacies from within a single organization, with the unit of randomization being the pharmacy. Pharmacies will be randomized to facilitated intervention based on the PARiHS framework or usual practice. The Alberta Context Tool will be used to establish the context of practice in each pharmacy. Pharmacies randomized to the intervention will receive task-focused facilitation from an external facilitator, with the goal of developing alternative team processes to allow the greater provision of medication management services for patients with diabetes, hypertension, and dyslipidemia. The primary outcome will be a process evaluation of the needs of community pharmacies to provide more clinical services, the acceptability and uptake of modifications made, and the willingness of pharmacies to participate. Secondary outcomes will include the change in the number of formal and documented medication management services in the aforementioned chronic conditions provided 6 months before, versus after, the intervention between the two groups, and identification of feasible quantitative outcomes for evaluating the effect of the intervention on patient care outcomes.

**Results:**

To date, the study has identified and enrolled the ten pharmacies required and initiated the intervention process.

**Conclusion:**

This study will be the first to examine the role of facilitation in pharmacy practice, with the goal of scalable and sustainable practice change.

**Trial registration:**

Clinicaltrials.gov identifier NCT02191111.

## Background

### The need for pharmacists to play a role in chronic disease management

Patients with diabetes, dyslipidemia, and hypertension are not achieving clinical targets as outlined in clinical practice guidelines [1–6]. It is well established that suboptimal control of these conditions increases patients’ risk of major complications such as myocardial infarction, heart failure, stroke, and kidney disease. As these conditions are primarily controlled using medications, adherence to prescribed therapies and appropriate dosing of these therapies become integral in helping to ensure patients achieve optimal outcomes.

Recent evidence from a number of systematic reviews [7–13] suggests that pharmacists’ management of patients’ medications yields improved use of, and adherence to, therapies. Additionally, the recent regulation of pharmacy technicians in Canada allows them to perform the final check on dispensed prescriptions [14]. This has created an opportunity for the greater delegation of this task, thereby freeing pharmacists to focus more specifically on patient care.

### What is holding pharmacists back?

Despite evidence of benefit and greater task flexibility, pharmacists are not providing medication management to all eligible patients with chronic conditions. Research into the reasons for this gap in the treatment of patients points to a number of barriers including a perceived lack of knowledge [15], confidence [16], time, and privacy [16, 17]. Some work also suggests that pharmacists are tied to traditional dispensing models of practice [15, 18, 19], and that the physical environment and workflow of the pharmacy are mainly dispensing-oriented [20].

Previous research into pharmacy practice change has focused on encouraging individual practitioners to drive the change [21], while failing to account for the influence of organizationally erected barriers within community pharmacy. A further assumption of this previous research has been that pharmacists possess the skills needed to identify and address these barriers, revealing what Rogers has called an individual-blame bias [22]. Pharmacists across Canada are interested in providing clinical services to their patients [18], but previous work in this area has neglected to provide instruction for how pharmacists can implement these changes.

### The Promoting Action on Research Implementation in Health Services framework

The Promoting Action on Research Implementation in Health Services (PARiHS) framework proposes three interrelated components as part of knowledge translation strategies: evidence, context, and facilitation [23, 24]. Each of these components must be optimized to ensure the successful implementation of evidence into practice and share a dynamic and simultaneous relationship with each other [25]. According to Kitson and colleagues [23], the most successful implementation occurs when the following criteria are met:

 *Evidence* is scientifically robust and matches professional consensus and patient preferences. The *context* is receptive to change, including sympathetic workplace culture, strong leadership, and appropriate monitoring and feedback mechanisms. *Facilitation* is provided to make the change process easier for group members, with input from skilled external and internal facilitators.

### Study objective/hypothesis

This paper outlines the protocol for a feasibility study of a facilitated pharmacy practice intervention based on the PARiHS framework. This intervention is intended to assist community pharmacists to increase the number of formal and documented medication management services completed for patients with diabetes, dyslipidemia, and hypertension, within a medium-to-large retail pharmacy chain organization. A cluster-randomized design will be utilized, as the knowledge translation intervention proposed may result in systemic changes in how pharmacies operate, thereby increasing the risk of contamination of the control group if a patient-level randomization were applied.

The objective of the study is to identify the needs of community pharmacies in implementing clinical services into practice, explore the acceptability and utility of facilitation in community pharmacy practice, and conduct a preliminary analysis on the outcomes of the intervention related to the number of services provided and patient care outcomes achieved. Should this feasibility study identify benefit, future work will involve the scale-up of the intervention across a greater number of pharmacies, with the ultimate goal of improving clinical care services provided to patients of community pharmacies.

## Methods/design

### Design

This will be a feasibility study with a cluster-randomized before-after design comparing ten pharmacies from within a single organization, with the unit of randomization as the pharmacy. Pharmacies will be randomized to facilitated intervention, based on the PARiHS framework, or usual practice in a 1:1 ratio. Ethics approval for the project has been obtained from the Health Research Ethics Board at the University of Alberta. Due to the nature of the intervention, blinding is not possible.

### Setting

The study will be conducted in community pharmacies (belonging to the same chain) in the province of Alberta, Canada. Our team has decided to work with a single organization to further ensure baseline consistencies among pharmacies, particularly relating to organizational structure, policies, and job descriptions.

### Participants

#### Pharmacists

Ten pharmacies belonging to the same pharmacy chain within the province of Alberta, Canada, will be identified for participation. Sites must have an interest in, and the ability to provide, medication management services but have not fully integrated these activities. No limitations on prescription count, location, or staffing level were applied. Rather, pharmacies were contacted and invited to participate until consent was received from the staff of ten pharmacies.

#### Patients

All Alberta residents eligible for the medication management services defined below can receive the services and will be counted towards the study outcomes. Intervention pharmacies will be encouraged to employ case finding strategies [26] to identify possibly eligible patients with diabetes, hypertension, and/or dyslipidemia. Case finding strategies use demographic information, as well as knowledge of condition-specific risk factors and symptoms to determine whether or not an individual would benefit from further testing or intervention [26]. By taking this approach to the identification of patient participants, scarce health resources will be saved as wholesale screening of the entire population of patients attending a particular pharmacy will be avoided.

### Randomization

The ten participating sites will be matched by an investigator not involved in enrollment or application of the intervention, into five most similar pairs based on geographic location, prescription volume, staffing level, and the existence of any specialty-certified pharmacists (e.g., Certified Diabetes Educators). However, prescription volume will form the primary matching variable, as time to conduct patient care services among other pharmacy activities has been identified as a key barrier preventing greater performance of these activities in North American pharmacy practice [27–29]. Using a random-number generator, one pharmacy from each pair will then be randomly allocated to either the intervention or control group. All regular staff of each pharmacy constitutes the members of that clustered site. Each regular staff member provided informed consent to participate prior to randomization.

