### Intervention

For the purposes of this project, it will be assumed that the evidence component of the PARiHS framework for the value of pharmacists’ intervention in the care of patients with diabetes, dyslipidemia, or hypertension is sufficiently optimized [7–13] and that pharmacists are aware of, and support, this evidence [18, 30].

External, task-focused facilitation [31], informed by an evaluation of contextual factors using the Alberta Context Tool (ACT), on-site observations, and participant interviews, will be applied to train community pharmacies to develop alternative team processes that enable a greater number of medication management services to be provided to patients with pre-specified chronic conditions [32]. Permissions to utilize the ACT have been received. This facilitation process will assist pharmacy team members in thinking through the change process and provide them with a set of skills to develop change strategies in the future. Facilitators will also serve as a liaison between management and front-line staff to implement potential organizational change processes to ensure alignment between expected service provision and the operational reality of pharmacy practice.

The facilitation process will begin with an evaluation of the contexts of all of the pharmacies using the ACT. Then, baseline rates of the completion of medication management services will be measured using pharmacy software. Facilitated discussions (i.e., participant interviews) will follow with pharmacy team members (managers, pharmacists, and technicians) to explore the scores of each of the dimensions on the ACT, and to develop strategies to address any barriers identified. All intervention pharmacy team members will also be asked to complete a facilitation evaluation survey.

From this, an alternative team process will be developed to provide pharmacy teams with guidelines for how more medication management services could be completed. These guidelines may include physical layout considerations, workflow improvements, patient identification strategies including case finding [26], task delegation from pharmacists to pharmacy technicians and assistants [33], and alignment of job description expectations between front-line staff and management.

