#### Secondary outcomes

**Service provision** To gauge the effectiveness of the intervention in improving medication management service provision rates, secondary outcomes will include descriptive analysis of the change in the number of formal and documented services in the aforementioned chronic conditions provided 6 months before versus after the intervention between the two groups. While the definition of medication management services varies in the literature, for the purposes of this study, they are defined as those services currently eligible for remuneration under the Alberta Pharmacy Services Framework [42] and include the following:

 Comprehensive Annual Care Plan (CACP) Standard Medication Management Assessment (SMMA) Follow-ups to CACP/SMMA Assessment and adaptation of a prescription Patient assessment for prescription renewal Patient assessment in a medication-related emergency (emergency prescribing) Optional services (those that can only be provided by pharmacists with additional certifications):

○ Assessment and administration of medications by injection

○ Patient assessment for initiating medication therapy

For the purpose of this study, service counts will be limited to the provision of a CACP, SMMA, or follow-ups to CACP or SMMA.

A CACP is designed to meet the unique needs of patients with complex health issues [42]. According to the Alberta Health Pharmacy Services Framework, ‘complex needs’ are defined as patients having at least two of the pre-identified chronic conditions or patients with at least one pre-identified chronic condition and one pre-identified risk factor (see Table 1) [42]. A CACP includes the completion of a patient assessment and a best possible medication history. This information is then used to develop a specific care plan to identify and resolve existing or potential drug-related problems, mutually develop therapy goals, and to follow-up and monitor the progress on identified goals. All information contained within the CACP is formally documented and provided to the patient and any other health professionals involved in the patient’s care, as needed. Prior to conducting a CACP, informed consent from the patient must be obtained.

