### Data collection

Process evaluation data will be collected over the course of the study. Results from the ACT will be collected at baseline and 6 months, as well as results from the facilitation evaluation surveys for intervention pharmacies. Interview data will be collected as they are conducted through the start-up phase of the intervention, and field notes will be collected continually as data collection for the primary outcome begins. All data will be stored securely at the University of Alberta Epidemiology Coordinating and Research (EPICORE) Centre.

Data on the change in the number of medication management services provided will be collected from pharmacy software programs located within the respective stores participating. Baseline numbers of medication management services provided will be counted back 6 months from the time of data collection (for example, if data collection begins May 1, 2014, pre-intervention data will be collected starting from November 1, 2013). Final data regarding the number of medication management services provided following the intervention will be collected for both intervention and control pharmacies for 6 months starting after the first set of in-person visits with the intervention pharmacies.

Data for the secondary clinical outcomes at baseline and 6 months will be collected at the same time as follow-up data for the primary outcome, for all patients receiving CACP or SMMA services. It is of key importance to note that pharmacist participants will not be asked to complete any data collection for the sole purposes of completion of the study. As the intention of this project is to improve the sustainability of clinical intervention provision by pharmacists, it is paramount that their actions herein are as close as possible to what they would be performing after the conclusion of the study. All clinical parameters will be reported by the pharmacies to the study investigators in aggregate form, without any patient identifying information. These values, and the frequency of their collection, will be analyzed descriptively to gauge whether potentially clinically meaningful changes can be reasonably assessed by this method.

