### Sample size

For this feasibility study, a pre-determined sample size of ten pharmacies (five intervention and five control) was decided upon as this was felt to be manageable by a single volunteer facilitator, and within the budgetary restrictions of our funding. The enrollment of five intervention sites is believed to be sufficient to initially detect common systemic organizational changes that may be of benefit to the pharmacy chain as a whole, while also allowing for refinement of the facilitation process for subsequent scale-up efforts. As the first study of this type in community pharmacies, the intracluster correlation coefficient (ICC) is unknown. A cluster-randomized trial of community pharmacies in Saskatchewan, Canada, estimated an ICC of 0.0143 [45]; however, it must be noted that data utilized to determine this value originated from various types of pharmacies (i.e., department mass-merchandise, chain-franchise, independent) [46]. One would expect our study to identify a higher ICC than reported in previous work due to our utilization of a single pharmacy chain for this study.

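### Pairing mainly on prescription volume balances the baseline service count only indirectly, and the planned difference in change is described without adjustment for that count

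*Protocol article*

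**What the plan says.** **Matching.** The Randomization section of the protocol article forms "five most similar pairs based on geographic location, prescription volume, staffing level, and the existence of any specialty-certified pharmacists". One of these leads: "prescription volume will form the primary matching variable, as time to conduct patient care services among other pharmacy activities has been identified" in earlier work as an obstacle to providing such services. Within pairs, "one pharmacy from each pair will then be randomly allocated to either the intervention or control group". The baseline service count is not listed.

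**Baseline count.** The Data collection section says that service counts "will be collected from pharmacy software programs located within the respective stores participating", and that the baseline is obtained by counting back six months. It therefore comes from existing records. The Intervention section places the measurement after the context survey: "Then, baseline rates of the completion of medication management services will be measured using pharmacy software". The Control section has it collected in that arm too.

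**Outcome and estimate.** The secondary outcome is a "descriptive analysis of the change in the number of formal and documented services in the aforementioned chronic conditions provided 6 months before versus after", restricted to CACP, SMMA and their follow-ups. The Statistical analysis section adds an effect size for the between-group difference in change, with a confidence interval. It uses this, together with acceptability and facilitator time, to judge whether scale-up is feasible. No baseline term is mentioned.

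**The concern.** Prescription volume stands in for one barrier, time. The Background section lists others: knowledge, confidence, privacy, attachment to dispensing and workflow. The number of services a pharmacy already delivers reflects all of them together, and it is the earlier value of the outcome itself. Entry does not fix the starting level: "Sites must have an interest in, and the ability to provide, medication management services but have not fully integrated these activities".

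Subtracting the baseline removes its influence only if change is unrelated to starting level. The Control section describes several concurrent shifts in Alberta pharmacy practice. If these raise services in proportion to what a site already does, the arm that starts higher gains more without any facilitation effect. If unusually high or low sites drift back, the error goes the other way. The estimate at stake is one of the inputs to the scale-up and cost-offset judgement.

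**Working it through.** The protocol gives no SD, effect size or correlation for service counts, and its sample size rests on feasibility and budget. There is no stated figure to reproduce. From the documents: ten pharmacies, five pairs, cluster-level analysis, difference in change. Everything else below is assumed.

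**1. How imbalance enters the estimate.** If the after count has slope b on the before count, and the arm baseline means differ by D, the difference in change with no intervention effect is (b − 1) × D.
- Proportional growth of 50%, arm means 60 and 30: (1.5 − 1) × 30 = 15 services (+30 against +15).
- Regression to the mean, b = 0.6, same means: (0.6 − 1) × 30 = −12 services.
- b = 1: zero. The change score is then fully protective.

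**2. How much baseline imbalance the pairing leaves.** Unmatched, the expected absolute difference in arm means is √(2/5) × √(2/π) = 0.50 between-pharmacy SD. Simulated pairing (normal counts, 40,000 replicates), with c the assumed correlation of the matching variable with baseline services:

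| Pairs formed on | Mean absolute imbalance (SD) |
|---|---|
| Volume, c = 0.3 | 0.49 |
| Volume, c = 0.5 | 0.45 |
| Volume, c = 0.7 | 0.39 |
| Volume, c = 0.9 | 0.28 |
| Baseline count itself | 0.19 |

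**3. What re-matching would gain in precision.** Settings: baseline count lognormal, median 40, log SD 0.7; log correlation with volume 0.2 or 0.5; log slope of after on before 0.6 or 1.0; log growth 0.1 to 0.4; noise SD 0.3. Matching on baseline count gave a standard error of 0.83–0.99 of that under volume matching, a gain of about 1 to 17%. With normal counts and c = 0.3, relative to no matching, volume pairing gave 0.98–1.01 and count pairing 0.78–1.01, mostly 0.9–1.0.

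A paired interval on 4 df is narrower than an unpaired one on 8 df only if the within-pair correlation of change exceeds 1 − (2.306/2.776)² = 0.31. In the normal-count settings, count pairing mostly stayed below that.

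**4. What adjustment would gain.** In the lognormal settings, a pharmacy-level regression of change on arm and baseline count, without pair terms, gave an SD of the estimate of 0.66–0.89 of the unadjusted value. The cost in the multiplier:
- Without pair terms, 8 to 7 df: 2.365/2.306 = 1.026.
- With pairs kept, 4 to 3 df: 3.182/2.776 = 1.146.

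Without pair terms, the rough net effect on interval width is 0.66 × 1.026 = 0.68 to 0.89 × 1.026 = 0.91. The simulated intervals were narrower than the unadjusted unpaired and paired ones in every setting. With pairs kept, the standard error would have to fall by more than 1 − 1/1.146 = 13% before the interval narrows, which is not assured.

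**The case against.** The case against is substantial, and most of it stands.

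- **The matching choice is reasoned.** The protocol explains why volume leads, and nothing is misstated or contradicted. A reader might infer that the pairing is an error or that the comparison is biased. Neither follows: allocation within pairs is random, so any imbalance is chance.
- **The change score already removes constant baseline differences.** True. Only slopes other than 1 matter, and the documents show neither proportional growth nor regression to the mean.
- **The simulations understate the actual pairing.** They match on volume alone. Staffing, location and specialty certification may also track service delivery, and at a volume-service correlation of 0.7 to 0.9 volume does visibly better.
- **A several-fold difference between matched sites is tempting to infer** from the open entry rule. The documents give no counts. They exclude fully integrated sites and use a single chain to promote consistency. Nor does an imbalance probability computed for unmatched allocation describe this design.
- **Re-pairing is closed.** The Trial status section says that all ten sites are enrolled and the intervention is being applied.
- **Adjustment may be set out in a fuller plan.** It may, and its absence from an article is not itself a fault. The point is narrower: the stated matching leaves this balance to chance to an unknown degree, and the stated estimate, as worded, does not compensate.

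What survives is the case for using baseline data that will be held anyway.

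**Conclusion.** The concern holds in a limited form. Pairing led by prescription volume balances baseline services only as far as volume and the other three variables track them. An unadjusted difference in change is exposed to whatever imbalance remains whenever change depends on starting level. The illustrative gaps of 15 and −12 services rest on assumed arm means of 60 and 30 and on assumed slopes; they are not estimates for this trial. The true size cannot be derived from the protocol.

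The documents do not support a claim that the pairing was wrong, or that matching on baseline count would have raised precision substantially. The more useful result is that adjustment without pair terms gave 0.66–0.89 of the unadjusted SD, under assumed lognormal settings. The weight is low: services are a secondary, descriptive outcome of a feasibility study whose primary outcome is process evaluation.

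**What to change.** Keep the allocation already made.

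1. Tabulate the baseline count of CACP, SMMA and follow-ups by pair and by arm.
2. Beside the unadjusted difference in change, report the pharmacy-level difference adjusted for baseline count, with its 95% interval. State whether pair terms are included.
3. For the scale-up study only, consider running the retrospective count before allocation and adding it to the matching variables. The price is somewhat looser matching on prescription volume.

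No new data are needed, since baseline counts are collected in both arms. The cost is one table, one extra estimate and one degree of freedom: 8 to 7 without pair terms (t from 2.306 to 2.365), or 4 to 3 with pairs kept (t from 2.776 to 3.182). With ten points, one outlying pharmacy can drive the fitted slope. The adjusted estimate should therefore stand alongside the unadjusted one and not replace it, and the table lets the reader see any such site.
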